### Inclusion and exclusion criteria

We will include patients who were older than 18 and were prescribed medicines in British National Formulary (BNF) category 4.10.2 (Nicotine Dependence) from 1 September 2006, when varenicline was introduced to the UK, to the present. We will use patients prescribed other smoking cessation products (nicotine patches, gum, lozenges, and inhalers) as controls for patients prescribed varenicline. We will include patients whose records were classified as ‘acceptable’ by the CPRD from all ‘up to standard’ general practices (GPs) at least 18 months prior to date of entry of each cohort (1st March 2005). Up to standard GPs are practices that have submitted data that meets the CPRD quality control thresholds. Patient data are defined as ‘acceptable’ by the CPRD if they meet minimum quality control standards, for example their registration period with their GP is valid.

We will exclude patients who registered at a GP less than 365 days before the first recorded prescription, to allow for high-quality assessment of baseline data and possible confounders. Patients prescribed bupropion in the year before their index prescription of varenicline or nicotine replacement therapy will be excluded from the analysis. In the primary analysis we will exclude patients initially prescribed nicotine replacement therapies and varenicline together, although in our previous analysis this only occurred for 0.25% of all prescriptions.^13^

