### Data analysis

#### Exposure measures

First time users of the smoking cessation therapies (varenicline or nicotine replacement therapy) will be defined as people who received at least one prescription of the product after the 1 September 2006 but with no use of a related product during the 12 months before the index date (the first date on which a prescription was issued). Langley *et al*^19^ found the smoking cessation prescription data in the THIN database, which is closely related to the CPRD, to be highly comparable to national dispensing data. The prescriptions will be defined by the therapy file in the CPRD, which contains a list of all prescriptions issued to patients by their GP. Each therapy record records the date a prescription was issued, the quantity of drug prescribed and the dose.

The primary analysis will be limited to the first treatment episode. This is analogous to an intention-to-treat analysis in a RCT.^20^ This ensures that the target parameter estimated in the observational study will be comparable to the parameter estimated by a RCT. For example, if patients’ treatment adherence and duration is related to whether they experience adverse events, then definitions of exposure which are based on treatment adherence may provide unreliable evidence of the causal effect of the prescription on adverse outcomes. This analysis framework was described in Hernán *et al* (2008). The intuition is that most randomised trials recruit individuals and then split participants into different treatment arms. This means that comparison groups are implicitly from first treatment. The primary analysis in an RCT typically reports an intention to treat estimate, which is the difference in allocation between arms of the trial based on allocation, rather than the treatment the participant received. To obtain results that are comparable to a randomised trial Hernán argued that analysts need to construct cohorts that also follow-up patients from first treatment, rather using retrospectively defined exposures (eg, retrospectively defining exposure as ever exposed to varenicline).

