To mimic an intention-to-treat analysis in an RCT, in our primary analysis patients who are initially prescribed nicotine replacement therapy, but later switch to varenicline, will be allocated to nicotine replacement therapy and vice-versa. We will use an intention-to-treat design for two reasons. First, while there are theoretical statistical models for estimating the effects of treatment switching such as marginal structural models, these methods require the strong assumption that there are no unmeasured confounders and typically require detailed data on time-varying confounders, which are unlikely to be available in the CPRD. Second, to our knowledge there are no instrumental variable methods to estimate the effects of switching treatment. However, we will investigate the number of participants who switch treatment as a sensitivity analysis.

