##### Follow-up

Follow-up will end with the earliest of either an ‘event’ or censoring due to the end of registration or death.

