### Socioeconomic variation in effectiveness of smoking cessation treatments

This project will use the entire sample of patients indicated as a smoker at any point after 1 September 2006. We will assign a measure of area level deprivation to each patient using their home address postcode and to each GP using the GP postcode. Deprivation levels will be based on the Indices of Multiple Deprivation (IMD), which are available from the ONS and are updated every 2 years. We will use the most recent IMD statistics preceding the date of entry into the study for each patient. Although area level deprivation statistics will only be a proxy for individual level deprivation, these demonstrate the expected associations with smoking prevalence.^41^ We will investigate whether the proportion of smokers who attend their GP for smoking cessation treatment differs by IMD, and whether there are any differences in prescribing of varenicline versus nicotine replacement products between areas of high and low deprivation.

By using individual and GP level IMD codes, we will investigate whether the effects of smoking cessation therapies differ by IMD at the level of GPs and at the individual level. We will investigate treatment compliance by reporting the total number of prescriptions issued after the initial prescription. We will estimate the effects of smoking cessation therapies within subgroups defined by IMD level at the individual and GP level using the three methods described above, multivariable-adjusted Cox regression, propensity score regression and instrumental variable analysis.^29^
^32^
^42^ The cohort of patients will be defined as described above. We will report these associations adjusted for basic confounders (age and gender), and results adjusted for all measured covariates described above. Analyses will account for clustering of patients by GPs.

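### Treatment compliance is defined as an open-ended count of later prescriptions, which mixes first-course adherence with re-treatment, switching and length of observation

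*Protocol article*

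**What the plan says.** The compliance measure appears once, under Socioeconomic variation in effectiveness of smoking cessation treatments: "We will investigate treatment compliance by reporting the total number of prescriptions issued after the initial prescription". It comes directly after the aim that "we will investigate whether the effects of smoking cessation therapies differ by IMD at the level of GPs and at the individual level", and directly before the plan to estimate effects within IMD subgroups.

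Four other statements bear on how the count would behave:

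- **Entry (Inclusion and exclusion criteria).** Prescriptions qualify "from 1 September 2006, when varenicline was introduced to the UK, to the present".
- **End of observation (Follow-up).** "Follow-up will end with the earliest of either an ‘event’ or censoring due to the end of registration or death".
- **Episode and switching (Exposure measures).** "The primary analysis will be limited to the first treatment episode", and "patients who are initially prescribed nicotine replacement therapy, but later switch to varenicline, will be allocated to nicotine replacement therapy and vice-versa". On switching, the article adds that "we will investigate the number of participants who switch treatment as a sensitivity analysis".
- **Data held (Exposure measures).** "Each therapy record records the date a prescription was issued, the quantity of drug prescribed and the dose".

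The first-episode limit is stated for the primary analysis. Nothing applies it to the compliance count.

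**The concern.** Compliance normally means how far a patient carried through the course that was started. A total of all later prescriptions measures something wider, for three reasons.

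1. A patient who stops early, relapses and begins again gains prescriptions from each new attempt, so failure of the first course can raise the score.
2. A patient who switches stays in the initial group, and prescriptions of the other product also follow the initial one. They are counted although they say nothing about persistence with the index product.
3. The count has no common end point, so a patient observed for longer has more time in which to accumulate prescriptions.

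The measure sits among the deprivation analyses, so a reader will probably use it when interpreting any difference in effectiveness by IMD. If the groups differ in re-treatment or in time observed, the count would show that difference under the label of compliance.

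**Working it through.** The article states no figure for compliance, so there is nothing to reproduce. The check has two parts: what the text lets into the count, and how the count behaves under stated assumptions.

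**What the text lets in**

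- *Time.* Entry opens in September 2006. The Power calculations add 4 years to data from 2006 to 2011, which puts the end of data at about 2015. Possible observation therefore runs from about 9 years for the first entrants to under 1 year for the last, less any deregistration or death. The 2015 end is an inference.
- *Re-treatment.* Outcome 1 reports that 74% of treated patients had a later smoking record and that 66% of these were current smokers: 0.74 × 0.66 = 0.49. About half of treated patients could therefore have reason to start again. How many did is not given.
- *Switching.* Switchers are to be counted, but their prescriptions of the second product are not removed from the total.

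**One patient against another (assumed numbers)**

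A patient with five further prescriptions in one completed course scores 5. A patient who stops after the first prescription and later starts three courses of three prescriptions scores 3 × 3 = 9.

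**Expected count**

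Total = c + r × p × (T − 0.25), where

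- c = further prescriptions in the first course,
- r = new courses per year,
- p = prescriptions per new course,
- T = years observed, with 0.25 years taken for the first course.

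The article gives none of these values. All are assumptions.

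*Same first-course behaviour, different observation time* (c = 1.0, r = 0.15, p = 2.0):

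- T = 2: 1.0 + 0.30 × 1.75 = 1.525
- T = 8: 1.0 + 0.30 × 7.75 = 3.325

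*Two deprivation groups.* Less deprived: c = 1.5, p = 2.5, r = 0.10. More deprived: c = 1.0, p = 2.0, with r = 0.10 or 0.20. A count confined to the first course gives 1.50 v 1.00.

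| Years observed | Less deprived (r = 0.10) | More deprived (r = 0.10) | More deprived (r = 0.20) |
|---|---|---|---|
| 1 | 1.69 | 1.15 | 1.30 |
| 2 | 1.94 | 1.35 | 1.70 |
| 4 | 2.44 | 1.75 | 2.50 |
| 8 | 3.44 | 2.55 | 4.10 |

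With equal rates the order never changes, but the gap moves from 0.50 to 3.44 − 2.55 = 0.89 at 8 years. With the rate doubled in the more deprived group, the order holds at 1 and 2 years and turns at 4 and 8.

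The rate at which the two totals are equal is r = (0.5 + 0.25 × (T − 0.25)) / (2.0 × (T − 0.25)). This gives 0.46, 0.27, 0.19 and 0.16 per year at 1, 2, 4 and 8 years, against 0.10 in the less deprived group.

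**The case against.** **This is a condensed article.** Windows and product rules are often left to a fuller document, and the article refers to a separate approved protocol (15_107). Its general design also leans towards restriction: a first-episode primary analysis, and windows of 3 to 48 months for service use and diagnoses. This has some force, but the article does more than stay silent. It states a measure, a *total* of what follows the initial prescription, and none of the restrictions elsewhere is extended to it.

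**The measure is descriptive.** This stands. The count enters no model, exposure or outcome. The Cox, propensity score and instrumental variable estimates follow the initial prescription and do not depend on it.

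**No comparison of compliance by IMD, or by product, is written.** This also stands. The comparison by IMD is implied by where the sentence sits, and no step is planned that would use compliance to explain differences in quitting.

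**Switching can be gauged.** This is partly right. The planned number of switchers would show how common the problem is, but it would not correct the count.

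**A stronger reading is tempting:** that the deprivation comparison will come out reversed, so that low compliance is wrongly dismissed as a reason for poorer quitting. The document does not support that. Reversal needs re-treatment or observation time to differ enough by deprivation, and no such figures are given. The Study aims report that more deprived smokers were more likely to receive cessation interventions. That concerns receiving treatment at all, not returning after relapse, so it is only weak support for the direction required.

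**Conclusion.** The point holds as a fault in a stated definition. The count mixes adherence to the first course, re-treatment, switching and time observed, and it cannot be read as compliance. That follows from the wording and needs no assumed rate.

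The size of the distortion is not known. On assumed rates, identical first-course behaviour gives a count more than twice as high at 8 years as at 2 (3.325 / 1.525 = 2.2). A reader might infer that the order of the deprivation groups is reversed. In the illustration this occurs only with a doubled re-treatment rate and long observation, and not with equal rates, so it is a possibility and not a finding. Unequal follow-up distorts an IMD comparison only if follow-up itself differs by IMD, which the article does not show.

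The consequence is confined to the interpretation of a descriptive result. The change is worth making because it is cheap and brings the measure into line with the first-episode and fixed-window design used elsewhere.

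**What to change.** Replace the sentence with a definition along these lines:

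- **Compliance:** the number of prescriptions of the index product, or days' supply where recorded quantity and dose allow, within one fixed window from the index date. The window is the same for all patients and is chosen by the investigators. Days' supply also avoids scoring one long prescription below several short ones that cover the same period.
- **Deregistration and death:** keep the window short, or use person-time within it.
- **Reported separately:** switching to the other product, and new courses after a gap, each at fixed windows or per person-year.
- **Presentation:** each of these by product and IMD level, stated as descriptive.

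No new data are needed, since the date, quantity and dose are in the therapy file. The cost is modest programming, cleaning of dose text (harder for gum, lozenges and inhalers), and a gap rule to separate one course from the next. Keeping only patients registered throughout the window would select slightly on survival and continued registration after the prescription. If that route is taken, the number excluded should be reported by product and IMD.

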**Methods:**

In this project we will investigate the effects of varenicline compared to nicotine replacement therapies on: (1) long-term smoking cessation and whether these effects differ by area level deprivation; and (2) the following clinically-important outcomes: rate of general practice and hospital attendance; all-cause mortality and death due to diseases of the respiratory system and cardiovascular disease; and a primary care diagnosis of respiratory illness, myocardial infarction or depression and anxiety. The study is based on a cohort of patients prescribed these smoking cessation medications from the Clinical Practice Research Datalink (CPRD). We will use three methods to overcome confounding: multivariable adjusted Cox regression, propensity score matched Cox regression, and instrumental variable regression. The total expected sample size for analysis will be at least 180 000. Follow-up will end with the earliest of either an ‘event’ or censoring due to the end of registration or death.

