### Study aims

What is the effect of varenicline on smoking abstinence? We will investigate the effects of varenicline on smoking abstinence because existing evidence from RCTs typically only followed participants for 1 year, and are not informative about long-term outcomes.What are the effects of varenicline on NHS service use? We will investigate the effects of varenicline prescriptions on all-cause primary and secondary care utilisation because smoking increases morbidity and imposes major costs on the healthcare services.^16^What are the effects of varenicline on all-cause and cause-specific mortality? We will investigate the incidence illnesses in the Clinical Practice Research Database (CPRD) using primary care diagnoses, admission to secondary care using ICD-10 codes, and Office of National Statistics (ONS) mortality records to maximise the number of events detected.What are the effects of varenicline on common physical and mental health conditions? We will investigate the effects of varenicline on rates of cardiovascular outcomes and respiratory illnesses, as previous research has suggested that patients prescribed varenicline may have different rates of these outcomes.^9^
^10^ Second, we will investigate the effects of varenicline on rates of depression and anxiety because there has been some reports that varenicline may reduce the risk of these outcomes.^13^We will also examine differences in smoking cessation medication effectiveness by socioeconomic position. A recent systematic review reported that stop-smoking services may be helping to reduce inequalities in smoking prevalence by preferentially targeting smokers of lower socioeconomic position (SEP). Data from primary care records The Health Improvement Network (THIN) show that between 2008 and 2010, smokers in more deprived groups were more likely to receive smoking cessation interventions.^17^

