### Power calculations

The following power calculations are based on effect sizes and CIs observed in our previously published results, which used data from 110 000 individuals prescribed either varenicline or nicotine replacement therapy.^13^ Based on the rate of 18 000 new prescriptions per year observed in the CPRD from 2006 to 2011,^13^ we estimate that with a further 4 years of follow-up the number of patients prescribed either varenicline or nicotine replacement therapy will have increased by 72 000. Therefore the total expected sample size for analysis will be around 180 000.

In our previous analysis using CPRD data the age-adjusted and sex-adjusted HR for self-harm/suicide for varenicline versus nicotine replacement therapy at 9 months was 0.73 (95% CI 0.54 to 0.99); after adjusting for possible confounders this became 0.90 (95% CI: 0.66 to 1.22).^13^ A 70% increase in sample size would lead to a reduction of the SE by a factor of 1.3, reducing the breadth of the above CI in the adjusted analysis from 0.56 to 0.43.

Rare outcomes, such as self-harm and suicide were used in previous analyses; in this project we will have greater power to explore more common outcome measures. For example, in the previous analysis the 9-month age-adjusted and sex-adjusted HR for all-cause mortality 9 months after first prescription for varenicline versus nicotine replacement therapy was 0.43 (95% CI 0.35 to 0.53); after controlling for possible confounders this became 0.49 (95% CI 0.40 to 0.61). A 70% increase in sample size would lead to a reduction of the SE by a factor of 1.3, reducing the breadth of the above CI in the adjusted analysis from 0.21 to 0.16.

For the effects of varenicline versus nicotine replacement therapy on all-cause mortality, instrumental variable analysis found a risk difference of 0.7 (95% CI −3.3 to 4.7) per 1000 patients treated after 9 months. We estimate that a 70% increase in sample size would narrow the CIs from 8.0 to 6.2.

Using data from our previous project, within 2 years of first prescription, we found 2517 admissions for respiratory disease among 1374 patients; 3144 admissions for cardiovascular disease among 1022 patients; and 3277 admissions for depression or anxiety among 213 patients. This is more events than we found for suicide and self-harm in our previous study; therefore we believe that there will be enough events for this analysis.

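### The aim of whether treatment effects differ by deprivation is paired only with separate IMD-subgroup estimates; no estimate or test of the difference is named

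*Protocol article*

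**What the plan says.** The question is stated three times. The Abstract (Methods) includes in its first numbered objective "long-term smoking cessation and whether these effects differ by area level deprivation". Study aims adds "We will also examine differences in smoking cessation medication effectiveness by socioeconomic position". The section on socioeconomic variation in effectiveness says "we will investigate whether the effects of smoking cessation therapies differ by IMD at the level of GPs and at the individual level". Each describes effect modification.

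The method is given later in that same section: "We will estimate the effects of smoking cessation therapies within subgroups defined by IMD level at the individual and GP level", using Cox regression, propensity score regression and IV analysis. The section also gives two adjustment sets (age and gender; all measured covariates) and says "Analyses will account for clustering of patients by GPs". It does not state the number of IMD groups, or how one group's estimate will be compared with another's.

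Power calculations deals with overall effects only. It gives no precision figure for the deprivation aim.

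**The concern.** Whether an effect differs between groups is answered by an estimate of the difference and its uncertainty. A list of group-specific hazard ratios or risk differences supplies the inputs and leaves the comparison to the reader. The usual shortcut is to note which groups reach significance and which do not. That can suggest a difference where none exists, and it can hide a real gradient when each stratum is imprecise. When every stratum is significant, the pattern of significance says nothing about a gradient.

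The article presents smoking as the principal cause of health inequalities and intends to send its findings to regulators. A claim that a medicine works in affluent but not in deprived areas, or a claim of no difference, should rest on a direct estimate.

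**Working it through.** **1. The article's own projections (Power calculations).**
- Sample size: 110 000 + 4 × 18 000 = 182 000, against "Therefore the total expected sample size for analysis will be around 180 000".
- Precision: "A 70% increase in sample size would lead to a reduction of the SE by a factor of 1.3"; √1.70 = 1.304.
- IV mortality risk difference at 9 months: the interval −3.3 to 4.7 per 1000 is 8.0 wide. 8.0/√1.70 = 6.14, and 8.0/√(182/110) = 6.22. The stated 6.2 is reproduced.

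**2. What stratifying does to precision.** Assume k equal, independent groups. The article gives no k, so 2 and 5 are shown. The subgroup SE is the overall SE × √k, and the SE of a difference between two groups is the overall SE × √(2k).

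| | k = 2 | k = 5 |
|---|---|---|
| IV mortality CI width per group, per 1000 (6.2 × √k) | 8.8 | 13.9 |
| IV mortality CI width for a two-group difference (6.2 × √(2k)) | 12.4 | 19.6 |
| SE of difference ÷ overall SE | 2.00 | 3.16 |

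These widths are for mortality. The article gives no IV precision figure for cessation.

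**3. How often significance would be mixed when the true effect is the same in every group.** With subgroup power p, P(mixed) = 1 − p^k − (1−p)^k.
- Overall power of 80% (an assumption) means an expected z of 1.96 + 0.84 = 2.80 overall and 2.80/√k per group. For k = 2, p = 0.508 and P(mixed) = 50%. For k = 5, p = 0.240 and P(mixed) = 75%.
- Self-harm/suicide, adjusted HR 0.90 (0.66 to 1.22), after the 70% increase: subgroup SE of log HR 0.170 (k = 2) or 0.269 (k = 5); P(mixed) about 17% or 30%.
- All-cause mortality, adjusted HR 0.49 (0.40 to 0.61), after the 70% increase: overall SE = [ln 0.61 − ln 0.40]/3.92/√1.70 = 0.083; subgroup SE 0.117 or 0.185; P(mixed) about 0% or 13%.

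**4. Cox analysis of cessation.** Outcome 1 reports that 74% have a later smoking record and that 66% of those are current smokers. 180 000 × 0.74 × 0.66 ≈ 88 000 relapse records, or about 17 600 per fifth. Assuming 1:1 allocation and no inflation for clustering, the SE of the log HR is about 2/√17 600 = 0.015 per fifth. At an assumed HR of 0.90, z = 0.105/0.015 ≈ 7 in every fifth, so mixed significance is very unlikely. The difference between two fifths has an SE of about 0.015 × √2 = 0.021. The ratio of hazard ratios would therefore be known to roughly ±4% (1.96 × 0.021 ≈ 0.042).

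**5. A formal comparison.** In simulation with no true difference, comparing the highest with the lowest of five estimates gave a nominal 5% difference in 28.5% of cases. A heterogeneity test (Cochran's Q, k − 1 df) on the same estimates rejected in 5.0%.

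**The case against.** The strongest reply has four parts.

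**Stratified estimates are a valid starting point.** With their SEs they yield a ratio of hazard ratios, a difference in risk differences, a Q test or a trend. They are also less restrictive than a single product term. This is correct. A reader might infer that subgroup estimates cannot show a difference, but that goes too far: the gap is that no contrast is named.

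**The article nowhere says that subgroups will be compared by significance.** This is also correct. The misreading is a risk that the text leaves open; it is not a stated plan.

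**A condensed article may leave the contrast to a fuller plan.** This lowers the weight of the point. It does not remove it, because the section already specifies both IMD levels, three estimators, the adjustment sets and clustering, and then stops before the quantity the aim asks for. Nor can the contrast always be rebuilt from published strata. Patients of one practice can live in areas with different IMD, so patient-level strata share practices and their estimates may be correlated. Comparing separate estimates ignores that covariance.

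**Chance differences need not be common for the outcome that matters.** A reader might infer that strata will usually disagree by chance. For example, five groups each with exactly 80% power give 1 − 0.8^5 − 0.2^5 = 67%. Neither the number of groups nor that power comes from the article. The Abstract attaches the deprivation question to cessation, for which Cox disagreement should be negligible. This part of the reply stands.

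**Conclusion.** The point holds in a limited form. The stated method stops one step short of the stated question: estimates within IMD groups are planned, and an estimate or test of their difference is not.

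The practical risk depends on outcome and method. It is real for the IV analysis and for outcomes with moderate overall power. It is small for Cox mortality (about 0% to 13% mixed significance) and negligible for Cox cessation. Even for Cox cessation, the size of any gradient and its interval still have to be reported to answer the aim.

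The figures assume two or five equal, independent groups. The IV widths concern 9-month mortality and serve only as an illustration. The documents do not support saying that the planned analysis is incapable of showing a difference, or that spurious differences are likely throughout. The point merits a change to the text at moderate priority.

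**What to change.** In the section on socioeconomic variation in effectiveness, state that any conclusion on differential effect will rest on a treatment-by-IMD interaction, or an equivalent between-group contrast or heterogeneity estimate, with its confidence interval and cluster-robust SE.

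- Fit it separately for patient-level and practice-level IMD.
- Do so in the Cox, matched Cox and IV analyses. In the IV model, instrument treatment × IMD with prior prescriptions × IMD and report instrument strength.
- State the number of IMD groups. If a one-degree-of-freedom trend is used, check linearity, since it can miss a non-linear pattern.
- Keep the subgroup estimates as description.

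The cost is some extra model terms on data already held and a check of covariate balance within IMD groups after matching. The IV interaction will probably be imprecise and should be reported as such.
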